#### Economic Evaluation

The EQ-5D-5L questionnaire will be used to obtain the health utility values for each participant before and after the intervention [32,34]. These values will be used to calculate the change in quality-adjusted life years (QALYs) over the 12-month follow-up for both groups [32,34]. The incremental cost-effectiveness ratio will be calculated as incremental cost divided by incremental QALYs. The willingness-to-pay per QALY threshold was set at 128,000 RMB (US $36,364) per QALY, equivalent to 1.76 times the gross domestic product per capita in China [35]. A 1-way sensitivity analysis will be conducted to assess the robustness of the model and the reliability of the results. All analyses will be performed using SAS (version 9.4; SAS Institute Inc).

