**Assessments**									
	Visit date	✓	✓	✓	✓	✓	✓	✓	✓
	Telephone follow-up for questionnaire administration			✓		✓		✓	
	Basic information	✓							
	Medical history	✓							✓
	Physical examination	✓							
	Pulmonary function test	✓							✓
AECOPD^b^ status		✓	✓		✓		✓		✓
SGRQ^c^		✓	✓		✓		✓		✓
TAI-10^d^		✓	✓		✓		✓		✓
EQ‑5D‑5L^e^		✓							✓
COPD^f^ medication use in the past 2 wk		✓	✓		✓		✓		✓
COPD medication regimen at current visit		✓	✓		✓		✓		✓
Other concomitant medications in the past 2 wk		✓	✓		✓		✓		✓
Treatment costs of COPD		✓	✓		✓		✓		✓
Disease status			✓		✓		✓		✓
Pharmacy service survey									✓

^a^CWPC: cough and wheeze pharmaceutical care.

^b^AECOPD: acute exacerbations of chronic obstructive pulmonary disease.

^c^SGRQ: St George’s Respiratory Questionnaire.

^d^TAI-10: Test of Adherence to Inhalers.

^e^EQ‑5D‑5L: European Quality of Life-5 Dimensions-5 Level version.

^f^COPD: chronic obstructive pulmonary disease.

Clinical pharmacists at intervention sites will receive standardized training before study initiation (Figure 1), including instruction on the trial rationale and objectives, COPD pharmacotherapy and inhaler use, and detailed guidance on implementing each intervention component. Pharmacists in the intervention arm will also be trained to use the digital inhaler sensor and the peak inspiratory flow rate assessment system to support inhaler use technique training (Figure 2) and device selection (see method 1 in Multimedia Appendix 1).

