##### Generic Quality of Life

Generic health status will be assessed using the EQ-5D-5L, which covers 5 dimensions (mobility, self-care, usual activities, pain or discomfort, and anxiety or depression), each rated on 5 levels from *no problems* to *extreme problems* [31]. We calculated the EQ-5D-5L index using the value sets developed by Luo et al [32], with 1 representing the value of instrument-defined full health. The main EQ-5D-5L outcome will be the between-group difference in change from baseline to 12 months in the utility index. Measurement time points are shown in Table 1.

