### Data Collection and Management

Outcome, baseline, and other trial data will be collected at prespecified time points (Table 1). Data sources include hospital medical records and participant-reported questionnaires, administered in person at baseline and months 1, 6, 9, and 12, and by telephone at months 3, 7, and 10. Data will be recorded in an electronic case report form and stored in the EDC system by trained site pharmacists. EDC access will be role based and password protected.

Data quality will be promoted through standardized training on questionnaire administration and electronic case report form completion, the use of predefined variable definitions and built-in logic checks in the EDC system, and routine source data verification by an independent pharmacist at each site, supplemented by periodic central data monitoring and query resolution by the coordinating center. Standardized and validated instruments (SGRQ, TAI, and EQ-5D-5L) will be used as described earlier, and study-specific forms (pharmacy service survey) are provided in Table S4 in Multimedia Appendix 1.

To promote retention and complete follow-up, appointment reminders will be sent via the WeChat mini-program, and missed visits will be followed up by telephone. Participants who discontinue or deviate from the assigned care pathway will be encouraged to remain in the study for outcome assessment.

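### The only uncertainty analysis named for the ICER is a 1-way sensitivity analysis, which cannot carry sampling error, cost-QALY correlation or clustering; with utilities at two time points, the comparison with 128,000 RMB per QALY has no valid statement of uncertainty

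*Protocol article*

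**What the plan says.** Utilities come from two occasions. The Economic Evaluation section states: "The EQ-5D-5L questionnaire will be used to obtain the health utility values for each participant before and after the intervention". The Generic Quality of Life section says "Measurement time points are shown in Table 1", and Table 1 ticks EQ-5D-5L at baseline and month 12 only. QALYs follow from these values: "These values will be used to calculate the change in quality-adjusted life years (QALYs) over the 12-month follow-up for both groups". No formula is printed. Then: "The incremental cost-effectiveness ratio will be calculated as incremental cost divided by incremental QALYs". The threshold is 128,000 RMB per QALY.

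Costs are microcosted per patient (Medical Cost section) and recorded at baseline and months 1, 6, 9 and 12. Hospitals are the unit of randomization.

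On uncertainty, the economic section offers one sentence: "A 1-way sensitivity analysis will be conducted to assess the robustness of the model and the reliability of the results". The other sensitivity analyses in the article, under Missing Data and Sensitivity Analyses, concern the SGRQ only.

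On the telephone contacts, Table 1 has a row "Telephone follow-up for questionnaire administration" ticked at months 3, 7 and 10. The Data Collection and Management section says questionnaires are "administered in person at baseline and months 1, 6, 9, and 12, and by telephone at months 3, 7, and 10". In those three columns Table 1 ticks only the visit date and the call itself, with no instrument.

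**The concern.** A 1-way analysis moves one input of a model between fixed limits while the rest stay put. Here no decision model is described. The inputs are two sets of measurements on the same patients, sampled within hospitals. What the reader needs to know is how far the cost and QALY differences, taken together, could have arisen by chance. If the plan is carried out as written, the article would place a point ICER on one side of 128,000 RMB and support it with an analysis that says nothing about that.

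The utility schedule adds a second uncertainty that no analysis can remove. Costs are followed through the year at five visits, whereas the denominator is interpolated between two. The intervention is delivered at baseline and months 1, 6 and 9, so a straight-line gain is one possibility among several.

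**Working it through.** The protocol prints no utility difference, incremental cost, QALY gain or ICER, so there is no stated figure to reproduce.

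**1. What the threshold comparison requires.** Write ΔC for incremental cost, ΔQ for incremental QALYs and λ = 128,000 RMB. Then

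- INB = λ·ΔQ − ΔC
- Var(INB) = λ²·Var(ΔQ) + Var(ΔC) − 2λ·Cov(ΔQ, ΔC)

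A 1-way analysis estimates none of these three terms. The mixed model planned for continuous secondary outcomes can give a cluster-aware interval for the utility index, hence for ΔQ alone. It does not give the covariance with cost.

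**2. Clustering.** The design effect is 1 + (m − 1)·ICC. The Sample Size section gives m = 15 and ICCs of 0.01 and 0.03 for the SGRQ. No ICC is given for costs or utilities, so borrowing these is an assumption.

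- ICC 0.01: 1 + 14 × 0.01 = 1.14, so standard errors rise by √1.14 = 1.07
- ICC 0.03: 1 + 14 × 0.03 = 1.42, so standard errors rise by √1.42 = 1.19

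An interval that ignored hospitals would be too narrow by those factors.

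**3. QALY gain by utility path.** Let d be the month-12 between-arm utility difference, with no difference at baseline. The gain is the area under the difference over one year.

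| Assumed path | Gain as a multiple of d | ICER relative to two-point area |
|---|---|---|
| Linear (the two-point area) | 0.5 × 1 = 0.50 | 1.00 |
| Full effect by month 1 | 0.5 × 1/12 + 11/12 = 0.958 | 0.50/0.958 = 0.52 |
| Full effect by month 6 | 0.5 × 6/12 + 6/12 = 0.75 | 0.50/0.75 = 0.67 |
| None until month 6, then linear | 0.5 × 6/12 = 0.25 | 0.50/0.25 = 2.00 |

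Taking the raw utility change as a full year of gain would give 1.00·d, exactly twice the two-point area, and would halve the ICER.

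**4. Illustration (d and ΔC are assumptions).**

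| | d = 0.04, ΔC = 4,000 RMB | d = 0.08, ΔC = 5,000 RMB |
|---|---|---|
| Two-point area | 4,000/0.020 = 200,000 | 5,000/0.040 = 125,000 |
| Full by month 1 | 4,000/0.0383 ≈ 104,300 | 5,000/0.0767 ≈ 65,200 |
| None until month 6 | 4,000/0.010 = 400,000 | 5,000/0.020 = 250,000 |
| Raw change | 4,000/0.040 = 100,000 | 5,000/0.080 = 62,500 |

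In the first column, the two-point area and the raw change fall on opposite sides of 128,000. In the second column both fall below it, and only the late path lies above. At d = 0.04, the two definitions disagree about the threshold only when ΔC lies between 128,000 × 0.020 = 2,560 and 128,000 × 0.040 = 5,120 RMB.

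**5. Baseline adjustment.** With two time points, QALY = 0.5·(u₀ + u₁₂). In a model that adjusts for u₀, the treatment coefficient for QALY is therefore half that for u₁₂, in the same complete cases and with the same covariates. The planned utility model thus already contains most of the adjusted QALY estimate.

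**The case against.** The strongest reply is that this is a condensed article. A QALY formula, a bootstrap and an acceptability curve commonly sit in an analysis plan that is not shown, and the general statement under Baseline Characteristics promises 95% CIs for effect estimates. The ICER is not among the objectives listed in the abstract, and the primary economic outcome is cumulative cost. A 1-way analysis is also a reasonable way to vary unit costs or the value set.

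Much of this stands. The absent formula is not a fault in itself, and the stakes are confined to the economic conclusion, since the primary SGRQ result is untouched. What it does not answer is that the article does name a method for judging robustness. That method is aimed at an undescribed model and cannot express the uncertainty that matters. The general promise of CIs does not mention the ICER or say how costs and QALYs would be handled jointly.

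A reader might go further and infer that the plan uses the raw utility change as the QALY gain, so that the denominator is wrong by a factor of two. The documents do not support this. A two-point area fits the wording, and the change in utility is defined separately as its own outcome: "The main EQ-5D-5L outcome will be the between-group difference in change from baseline to 12 months in the utility index". Nor is two a bound: the error is nil if the path is linear and the area is used, and other paths give other ratios.

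A reader might also infer that the telephone calls carry no questionnaire. The text says that questionnaires are given then. Table 1 simply does not say which.

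**Conclusion.** The point holds for the uncertainty analysis and for the reliance on two utility measurements. The 1-way analysis supplies no sampling error, no cost-QALY covariance and no allowance for hospitals, so the ICER would be set against 128,000 RMB without a valid statement of uncertainty. The two-point area rests on a linear path that the data cannot test. Under the assumed paths in the table, the gain runs from 0.25 to 0.96 times the month-12 difference, against 0.50 for the area. The ICER would then be between about half and twice its two-point value. These are scenarios, not estimates. Whether the threshold conclusion changes depends on a utility difference and a cost difference that the documents do not give.

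The mismatch over the month 3, 7 and 10 calls is a real inconsistency, but it is separate and does not itself affect the ICER.

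**What to change.** 1. Add a bootstrap that resamples hospitals within arm (respecting the secondary and tertiary strata where numbers allow) and keeps each patient's cost and QALY paired, or an equivalent cluster-aware bivariate model. Report a 95% CI for incremental net benefit at 128,000 RMB and an acceptability curve. Keep 1-way analyses only for inputs such as unit costs or the value set.
2. Define incremental QALYs as the area under the utility curve, adjusted for baseline utility with a site effect, and with utility zero from death. State that the raw utility change is not used as the QALY gain.
3. State that two time points impose a linear path, and show the ICER under an early path (about 0.96 times the month-12 difference) and a late path (0.25 times) beside the two-point result.
4. Reconcile Table 1 with Data Collection and Management on which questionnaire is given at months 3, 7 and 10.
5. Optionally, add EQ-5D-5L to remaining contacts, in both arms alike, and treat it as supportive. Enrollment closed on December 31, 2025, so participants already past those contacts will lack it. It would also mean changing the schedule and data-capture forms at 34 sites.

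Items 1 to 3 need analysis-plan wording and some extra programming, with no new data. Their downside is a less definite cost-effectiveness statement.

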### Data Monitoring and Quality Assurance

The trial will be overseen by a steering committee convened by the coordinating center (China-Japan Friendship Hospital), comprising clinical experts in COPD, pharmacologists, and epidemiologists. Given the low-risk nature of the intervention (pharmacist-led care enhancement) and the absence of planned interim efficacy analyses, a separate data monitoring committee will not be established. Trial monitoring will be conducted by the coordinating center’s monitoring team, which is independent of site investigators and reports to the steering committee.

The EDC system will automatically validate the input data. If the recorded values fall outside the acceptable range, a prompt will appear, requesting the user to double-check the entry. Each research center will have an independent pharmacist responsible for conducting source data verification. Additionally, the lead organization will provide real-time reminders to each center regarding participant enrollment and follow-up implementation plans. If any issues are identified during monitoring visits, the lead team will assist the site in resolving them. The lead organization will also conduct audits to assess the overall quality and completeness of the data, review source documents, interview investigators and coordinators, and ensure that clinical centers comply with the study protocol requirements.

Because the intervention is a pharmacist-led care enhancement, it is expected to pose minimal risk, and serious adverse events are unlikely. Nevertheless, potential risks will be reviewed throughout the trial. Study staff will be trained to identify and document any adverse events and to report them in accordance with each hospital’s standard procedures and ethical requirements.

### Ethical Considerations

This project has received approval from the Clinical Research Ethics Committee at the China-Japan Friendship Hospital, China, on May 20, 2024 (2024-KY-154). Researchers will provide participants or their legal representatives with an easily understandable informed consent form, approved by the ethics committee and allow them sufficient time to consider participation. Participants may not be enrolled in the study until a signed consent form is obtained from the participant or their legal representative. During the study, participants will be provided with all updated versions of the consent form and any relevant written information. The informed consent form will be retained as an essential document of the clinical trial for future reference.

All participant data were de-identified in the EDC system. Specifically, participants were identified using unique numerical codes rather than full personal identifiers. Each participant received compensation of CNY 200 (USD 28.66) for their time and travel expenses associated with study participation. Participants were informed during the informed consent process that they had the right to withdraw from the study at any time, for any reason, and without penalty.

### Dissemination Policy

The study findings will be disseminated to participating pharmacists, referring physicians, patients, and the broader medical community through peer-reviewed publications.

## Results

### Overview

The trial was registered on July 15, 2024 (ChiCTR2400086943). The study was funded in December 2024. Recruitment started on November 15, 2024, and enrollment was completed by December 31, 2025. As of December 31, 2025, we enrolled 454 participants, of whom 16 (3.5%) had completed the 12-month follow-up. The trial is expected to be completed by December 31, 2026, with results expected to be published in 2027 (Figure 1).

### Trial Status

The trial enrollment was completed by December 31, 2025, and the trial is now in the follow-up stage.

## Discussion

### Anticipated Findings

COPD remains a major public health challenge. The GOLD guideline highlights the importance of patient education, with particular emphasis on appropriate inhaler use technique and adherence to regular maintenance therapy [6]. Despite these recommendations, suboptimal disease control often persists due to 3 interrelated issues: medication nonadherence, inappropriate inhaler use technique, and inappropriate device selection [7-11]. These shortcomings not only exacerbate symptoms and hasten disease progression but also diminish HRQoL and increase health care facility use [12-14]. Against this backdrop, this study seeks to determine whether a multifaceted, pharmacist-led intervention, supported by digital tools and based on the IMB model, can mitigate these challenges in routine care. We anticipate that our digital-enabled pharmaceutical care program, which combines structured, IMB-guided pharmaceutical care with digital support via a WeChat mini-program and inhaler-integrated digital sensors, might yield clinically significant improvements in HRQoL.

### Comparison With Previous Work

Previous research has shown that pharmacist-led interventions can enhance critical aspects of inhalation therapy, including medication adherence and inhaler use technique [15-20]. IMB-based strategies have further demonstrated improved adherence in other chronic disease contexts by emphasizing clear information, meaningful motivation, and practical behavioral skills [21,22]. In this study, the *information* component involves interactive question-and-answer sessions, visual aids, and online educational resources designed to facilitate accessible and comprehensible knowledge. The *motivation* component enhances patient autonomy through regular follow-ups, feedback, and reinforcement of self-efficacy. The *behavioral skills* component underscores standardized training, digital sensor–based reminders, and real-time corrective guidance, all aimed at sustaining appropriate medication practices by promoting both correct medication administration and device appropriateness. Each of these 3 IMB dimensions is reinforced by quantifiable evaluation metrics, helping pharmacists deliver more precisely targeted management and education.

Meanwhile, digital tools such as real-time adherence monitoring and telehealth modules hold promise for improving self-management and HRQoL in patients with COPD [23-26]. In this intervention, *inhalable drug digital sensors* provide voice prompts to guide patients in the correct use of inhalers and record real-time inhalation behaviors. Pharmacists can intervene promptly when they identify incorrect use or recommend more suitable inhalation devices. In addition, the study expands beyond traditional face-to-face consultations by offering health knowledge updates, allowing participants to access project-specific information on COPD and medication use at home rather than in person. This approach leverages emerging technologies to establish a new model for pharmacist-led, multifaceted services and lays the groundwork for future digitally integrated pharmaceutical interventions.

### Strengths and Limitations

This trial has several anticipated strengths. It uses a multicenter, cluster randomized design across secondary and tertiary hospitals, which enhances external validity in higher-level care settings and reduces contamination between the intervention arm and control arm. The intervention is explicitly theory driven, grounded in the IMB model, and delivered by pharmacists who receive standardized training, which supports both intervention fidelity and future scalability. Furthermore, the study uses a comprehensive set of outcomes, including the SGRQ, TAI-10, EQ-5D-5L, and a pharmacy service survey, to capture not only clinical and behavioral effects but also patient-reported experiences with pharmacist-led care.

However, this study also possesses some limitations. First, our findings mainly reflect patients with COPD attending secondary and tertiary hospitals whose inhaler use technique is suboptimal and who are matched to an appropriate inhaler device, which may limit the generalizability of the results to other care settings. Future investigations should explore primary care settings to validate the intervention’s impact across multiple levels of the health care system. Second, we did not measure participants’ digital literacy, which could understate differences in engagement or create suboptimal outcomes among individuals who are less comfortable with technology. Finally, because this is a complex pharmacist-led behavioral intervention, neither the content nor the intensity of care can be fully masked to participants. Although the trial was registered as *single blind*, participants in the intervention arm are likely to be aware of receiving additional education and digital tools, and the primary and key secondary outcomes are all patient reported (SGRQ, TAI-10, EQ-5D-5L, and the pharmacy service survey). This may introduce performance and reporting bias. To mitigate this limitation, we used cluster randomization at the clinic level, applied an identical follow-up schedule and basic medication education and inhaler use training in both arms, and blinded the outcome assessors and statisticians.

### Conclusions

By facilitating the deep involvement of pharmacists in the medication management process for patients with COPD, the goal of the study is to improve medication adherence and correct inhaler use, thereby enhancing patient outcomes and reducing the disease burden associated with COPD. The study findings will be shared through peer-reviewed publications. If the study results demonstrate a positive impact of this digitally enhanced, multifaceted pharmaceutical intervention on COPD prognosis and disease burden, they will support the widespread adoption of this pharmaceutical management model in more than 1000 CWPC clinics across China, offering a novel approach to medication management for patients with COPD.

## Appendix

Multimedia Appendix 1 Trial stages, digital inhaler training, and trial registration dataset.

Multimedia Appendix 2 Trial registration: dataset.

## Abbreviations

COPD: chronic obstructive pulmonary disease
CWPC: cough and wheeze pharmaceutical care
EDC: electronic data capture
GOLD: Global Initiative for Chronic Obstructive Lung Disease
HRQoL: health-related quality of life
IMB: information-motivation-behavioral skills
QALY: quality-adjusted life year
SGRQ: St George’s Respiratory Questionnaire
SOP: standardized operating procedure
SPIRIT: Standard Protocol Items: Recommendations for Interventional Trials
TAI-10: Test of Adherence to Inhalers
